**Background**

Through the collaboration of the UHB, DSTL and University of Birmingham we wish to characterise the biomarker response to traumatic brain injury and define the roles of biomarkers relating to injury detection, diagnosis, monitoring, classification, prognosis and treatment. This will form a basis for future interventional studies to improve outcome from traumatic brain injury.

This study draws from two previous studies, Biomarkers of Brain Injury and Steroids and Immunity from Injury through to Rehabilitation study. The former aimed to identify novel biomarkers in a severe brain trauma population; the latter included a sub-population of severe brain trauma and looked at a small range of biomarkers. The major weaknesses in both of these studies were a limited appraisal of outcome following brain trauma as opposed to severity at inclusion and limited follow-up of participants. We aim to build on these studies with a broader population and comprehensive assessment of outcome.

Studies carried out have not fully defined the role of biomarkers in clinical practice; few have made a transition to routine practice.

*Traumatic Brain Injury (TBI)*

There is increasing interest in TBI and it remains a leading cause of morbidity and mortality in particular affecting the young with a male preponderance. Although previously reported to be an untreatable cause of mortality there have been improvements, particularly when treatment is given in specialist neurosurgical centers irrespective of need for surgical intervention as recommended by NICE in the UK. At present treatment is largely supportive and investigational techniques have not changed apace clinically with the research field.

*Biomarkers in Brain Injury*

A biomarker in the broadest sense is any characteristic that may be objectively assessed to provide an indicator of a normal or abnormal disease or physiological state of an organism, this includes imaging and laboratory tests along with more simple clinical findings. Biomarkers are used in other clinical settings such as Troponin for cardiac damage.

There has been much interest in the development of biomarkers for neuro-trauma though this has yet to lead to a change in clinical practice. Previous research has assessed potential biomarkers, for instance Creatine kinase, glial fibrillary acidic protein, myelin basic protein and S100B. S100B has been the most intensely studied and has since been shown not to be specific to CNS damage.

CT remains the mainstay imaging technique in the acute phase of assessment for brain injury though has a limited ability to demonstrate pathology, MRI has increased sensitivity for some aspects of trauma but both are outstripped by a host of new techniques. Diffusion Tensor Imaging (DTI) is a development of MRI relying on standard equipment with different processing techniques. It has much improved sensitivity for axonal injury, the hallmark of TBI. Regarding laboratory markers, these are substances released generally in response to or as an effect of injury in this context and may be assayed in order to provide an insight into many factors surrounding an injury, such as severity.

This study aims to improve on previous clinical studies by investigating a range of potential biomarkers in serum, diasylate, CSF and imaging in brain injured and non-brain injured (control) trauma patients with comprehensive outcome measures. The benefits to patients enrolled in this study are minimal.

In the long term we hope these biomarkers might improve the diagnosis, monitoring and prognostication of brain trauma thus allowing better targeted treatment and potentially revealing new avenues of treatment.

**Aim**

To characterise the relationship between biomarkers, brain injury severity and outcome.

**Hypotheses**

The hypothesis to be tested is that biomarkers of neurotrauma may give specific prognostic information for an individual patient to inform acute and sub-acute treatment stratification and future prognosis. Measurements of biomarkers taken after trauma will be correlated with outcome measures at 6 and 12 months.

Secondary hypotheses are that novel biomarkers exist and may be identified; genetic factors are important modulators of outcome.

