**Study Design**

This is a cohort study to categorise the traumatic brain injury population at UHB. Brain biomarkers, serum, micro-diasylate, CSF and imaging will be measured in two groups of patients. Outcome will be assessed by TMS threshold, ERP, ERG, VEP and cognitive and psychological questionnaires will be performed. The two groups of patients will be:

The study group - patients who have suffered a head injury presenting or transferred to UHB.

The control group - patients admitted with non-head trauma matched to the study group by ISS severity and demographic.

Patients for inclusion will be identified at point of injury or as soon as possible after presentation to UHB upto 1 hour post injury. For samples taken pre-hospital where patients are unable to consent these will be taken, subject to a favourable REC opinion under the Mental Capacity Act ‘waiver’ for research in emergency situations. Advice will be sought from a consultee as soon as practicable following presentation to hospital and consent will be sought from the patient once capacity has been regained. Information in the form of the included Patient Information Sheets or Consultee Information Sheet will be provided; consent or advice will be recorded on the appropriate written forms annexes c-i.

*Inclusion criteria:*

Study group - Patients who have sustained a head injury resulting in presentation to UHB within 1 hour of injury.

Control group - non-head trauma patients matched to control by severity (ISS) and demographic.

*Exclusion criteria:*

Children under the age of 18 years. For the control group those with a recent head injury or known neurological condition.

Our conservative assumption is that 80% of head injured patients will show a positive biomarker response with 10% of non-head injured patients showing a positive response. Using fishers Exact test (power0.9; alpha 0.05; 1:1 control subject ratio) would predict 10 patients in each group. However head injuries and trauma in general demonstrates much heterogeneity and to allow comparison across modalities and sub-groups we intend to recruit up-to 100 patients to the study group and the control group.

*Sampling - Blood*

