**Statistical Analysis**

Data will be analysed using SPSS. Descriptive statistics will be determined on parametric and non-parametric data. The independent variables are age, sex, ISS/NISS, type of injury, MTOR activity status. The primary dependent variables include biomarker levels, imaging analysis, TMS threshold and cognitive/psychological scoring. Exploratory assessment of data will be completed using analysis of co-variance and ordinal analysis of outcome. The spread of the means will be given as standard error of the mean. Differences in the means are considered significant if p<0.05. Psychological and cognitive scoring will undergo correlation analysis using Spearman’s rank correlation coefficient. They will also be subject to Rasch analysis. Multivariate regression analysis will be used to identify factors with significant impact on outcome.

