**Outcome Measures**

Outcome of brain trauma will be assessed with cognitive and psychological symptom scoring, TMS threshold measurement and ERP. Initial severity scoring will be assessed with ISS/NISS. Changes in biomarkers will be measured in relation to brain trauma versus non-brain trauma and related to the above outcome assessment.

The primary outcome will be functional status as measured by the Glasgow Outcome Score at 6 months. Secondary outcome measures are functional status as assessed by the Glasgow Outcome Score at 12 months; cognitive and psychological symptom scoring with Post­concussion Symptom Questionnaire­19 (PCSQ­19), Impact of Events Scale – revised (IES­r), Depression and Anxiety Symptom Scale – 21 (DASS­21), PTSD checklist (PCL), Patient Health Questionnaire (PHQ), neurological assessment battery NAB-SM.

Other seconday outcome measures are neurophysiology measures of TMS threshold and Event related potentials.

Developing a better understanding of the relationships surrounding severe brain trauma and biomarkers in development will lead to better clinical understanding, categorisation, prognostication and treatments, both in targeting existing interventions and through development of new treatment in future interventional studies.

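### The prognostic hypothesis is about the individual patient, but the analyses stated for it measure only average association, so a significant result would not support the stratification claim

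*Protocol*

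**What the plan says.** The Hypotheses section of the Protocol states the main hypothesis at the level of one patient and ties it to treatment decisions: "biomarkers of neurotrauma may give specific prognostic information for an individual patient to inform acute and sub-acute treatment stratification and future prognosis". The sentence that follows says how it will be examined: "Measurements of biomarkers taken after trauma will be correlated with outcome measures at 6 and 12 months".

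The Statistical Analysis section lists these methods that could link markers to outcome:
- "Exploratory assessment of data will be completed using analysis of co-variance and ordinal analysis of outcome"
- "Psychological and cognitive scoring will undergo correlation analysis using" Spearman's coefficient (Rasch analysis of the same scores is also planned)
- "Multivariate regression analysis will be used to identify factors with significant impact on outcome"

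The only threshold in that section is "Differences in the means are considered significant if p<0.05".

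Under Outcome Measures, "The primary outcome will be functional status as measured by the Glasgow Outcome Score at 6 months". On size, Study Design says "we intend to recruit up-to 100 patients to the study group and the control group". The Aim section is more modest than the hypothesis: it seeks only to characterise how biomarkers, severity and outcome are related.

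**The concern.** A correlation, a difference in means and a significant regression coefficient all answer the same kind of question: does outcome shift, on average, with the marker? The hypothesis asks something else: does the marker say enough about one patient to guide how that patient is treated? With a moderate sample the first answer can be yes while the second is no.

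The Protocol fixes both the hypothesis and the method in adjoining sentences, and they do not match. The Background section presents the study as a basis for later interventional studies. If a significant but weak correlation is read as support for the hypothesis as worded, a marker that misses most poor-outcome patients could be carried forward as a stratification tool.

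**Working it through.** **1. The plan's own figure.** The only calculation in the Protocol is in Study Design: 80% against 10% marker-positive, Fisher's exact test, power 0.9, alpha 0.05, 1:1, giving 10 per group. Exact enumeration gives one-sided power of 88.8% at 9 per group and 93.7% at 10, so 10 is reproduced. Two-sided power is 84.1% at 10 and 90.5% at 11. This calculation concerns separating head-injured from other trauma patients. It is not about prognosis, so it does not bear on the hypothesis examined here.

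**2. What becomes significant at n = 100.** A correlation tested against zero, two-sided at 0.05, is significant when |r| exceeds tanh(1.96/√(100 − 3)) = tanh(0.199) = about 0.20. That is 0.20² = 4% of variance.

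**3. Inputs for the simulation.**
- From the Protocol: up to 100 head-injured patients; Glasgow Outcome Score at 6 months; p<0.05.
- Assumed: two-sided test; all 100 analysable (70 as an alternative); a five-level outcome with cumulative cuts at 15, 17, 30 and 50%; unfavourable = lowest 30%.
- Model: latent outcome y = ρx + √(1 − ρ²)·e, with marker x and error e standard normal. y is cut into five levels and Spearman's test is applied.

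**4. Results at n = 100.**

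| Latent ρ | Significant | AUC for unfavourable outcome | Sensitivity at 90% specificity |
|---|---|---|---|
| 0 | 5% | 0.50 | 10% |
| 0.20 | about 40% | about 0.60 | 17% |
| 0.25 | about 56% | 0.62 | 19% |
| 0.30 | about 76% | 0.64 | 22% |
| 0.35 | 86% | 0.67 | about 25% |
| 0.40 | 94% | 0.69 | 27% |

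Other assumed five-level distributions give 72–78% at ρ = 0.30 and 40–43% at ρ = 0.20. With 70 analysable patients, the figure at ρ = 0.30 is about 58% (56–61% across assumed distributions), and at ρ = 0.20 about 30%.

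**5. What ρ = 0.30 means for a patient.**
- Variance explained: 0.30² = 9%.
- Narrowing of an individual prediction interval: 1 − √(1 − 0.09) = 4.6%.
- At 90% specificity, 100 − 22 = 78% of poor-outcome patients are missed. Overall error is 0.7 × 0.10 + 0.3 × 0.78 = 0.07 + 0.234 = about 30%, the same as calling every patient favourable.

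**6. Precision of the alternative measure.** For AUC 0.65 with 30 poor and 70 good outcomes, the 95% interval is about 0.53 to 0.77.

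**The case against.** **No decision rule is written.** The Protocol never says that the hypothesis is supported when a correlation differs from zero. Its one threshold is worded for means, and Spearman's coefficient is named for the psychological and cognitive scores, not for the Glasgow Outcome Score. This stands: the zero null is an inference from the default use of these methods and from the lack of any other criterion. The point therefore concerns what the stated analyses can support, not a written rule that is wrong.

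**Discrimination and calibration may be in the SAP.** Ordinal or multivariable regression gives predicted probabilities from which both can be computed, and nothing excludes this. Their absence alone would be no finding. What remains is the mismatch between the hypothesis and the method that the Protocol sets beside it.

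**The claim is hedged.** The hypothesis says only that markers may give such information, part of the analysis is called exploratory, and the Aim concerns a relationship. Association is a reasonable first step for a cohort. This narrows the point to the individual-patient and stratification wording.

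**Stronger readings that a reader might infer, and that do not hold:**
- That such a marker would misclassify most patients. At ρ = 0.30 overall error is about 30%; what it misses is most of the poor-outcome patients.
- That significance in 40–76% of studies is an inflated false-positive rate. Those correlations are real, so this is power. The test rejects in about 5% at ρ = 0, as it should.
- That a weak marker will usually be significant. For a single marker and outcome this fails at ρ = 0.20 with 100 patients, and at 0.25 with 70.
- That no stated result could count against the hypothesis. A correlation near zero would.

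**Conclusion.** The concern holds in a limited form. The Protocol states an individual-patient, treatment-stratifying hypothesis and sets against it methods that measure average association. A significant result from those methods would support association and would leave the individual-level claim untested.

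The gap is widest for modest markers: at a latent correlation of 0.30, significance is likely with 100 analysable patients but more than three-quarters of poor-outcome patients are missed at 90% specificity. The chance of significance falls if fewer patients are analysable, which is plausible because 100 is an upper limit and the Protocol recognises possible loss to follow-up.

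These sizes rest on the bivariate normal model, the assumed outcome distribution, the 30% unfavourable rate and a single marker. None of these is given in the Protocol. The mismatch itself needs no assumption. It should be corrected, but it does not undermine the study's use for describing association.

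**What to change.** Choose one of two changes, in the Hypotheses and Statistical Analysis sections.

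1. **Keep the individual-patient hypothesis and match the analysis to it.** For the early markers, report the AUC or ordinal c-index for the 6-month Glasgow Outcome Score in head-injured patients, with a 95% confidence interval and bootstrap optimism correction. Add calibration for any multivariable model. State that any conclusion about individual prognosis or stratification rests on these results, and that correlations describe association only.
2. **Restate the hypothesis as association** between early markers and outcome, in line with the Aim, and leave individual prediction to later work.

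The first option needs a few sentences and a little more analysis of data already being collected. Its price is wide intervals at 100 patients or fewer (about ±0.12 around an AUC of 0.65 with 30% unfavourable outcomes) and fewer markers that can be called individually prognostic. The second costs only wording, but gives up the stronger claim. No AUC pass mark is proposed: the Protocol offers no basis for a value, and at this sample size a strict limit could reject useful markers.

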**Clinical Setting**

University Hospital Birmingham is a fast developing major trauma centre and tertiary referral neurosurgical centre seeing a large number of both TBI and general trauma casualties from across the West Midlands. The latter group providing non-head injury comparison. Analysis for biomarkers will be performed at the University of Birmingham and DSTL.

**Study Design**

This is a cohort study to categorise the traumatic brain injury population at UHB. Brain biomarkers, serum, micro-diasylate, CSF and imaging will be measured in two groups of patients. Outcome will be assessed by TMS threshold, ERP, ERG, VEP and cognitive and psychological questionnaires will be performed. The two groups of patients will be:

The study group - patients who have suffered a head injury presenting or transferred to UHB.

The control group - patients admitted with non-head trauma matched to the study group by ISS severity and demographic.

Patients for inclusion will be identified at point of injury or as soon as possible after presentation to UHB upto 1 hour post injury. For samples taken pre-hospital where patients are unable to consent these will be taken, subject to a favourable REC opinion under the Mental Capacity Act ‘waiver’ for research in emergency situations. Advice will be sought from a consultee as soon as practicable following presentation to hospital and consent will be sought from the patient once capacity has been regained. Information in the form of the included Patient Information Sheets or Consultee Information Sheet will be provided; consent or advice will be recorded on the appropriate written forms annexes c-i.

*Inclusion criteria:*

Study group - Patients who have sustained a head injury resulting in presentation to UHB within 1 hour of injury.

Control group - non-head trauma patients matched to control by severity (ISS) and demographic.

*Exclusion criteria:*

Children under the age of 18 years. For the control group those with a recent head injury or known neurological condition.

Our conservative assumption is that 80% of head injured patients will show a positive biomarker response with 10% of non-head injured patients showing a positive response. Using fishers Exact test (power0.9; alpha 0.05; 1:1 control subject ratio) would predict 10 patients in each group. However head injuries and trauma in general demonstrates much heterogeneity and to allow comparison across modalities and sub-groups we intend to recruit up-to 100 patients to the study group and the control group.

*Sampling - Blood*

Sampling of blood will be performed at regular intervals beginning at point of injury through to follow-up at six months post injury. During emergency treatment at point of injury venous access is gained to allow the delivery of drugs and fluids. Blood samples are not usually withdrawn as there are no current clinical investigations available at that time-point. We propose to withdraw 20mls of venous blood for early biomarker analysis. Blood samples are taken routinely over the following days of admission to monitor various factors, where feasible research samples will be withdrawn alongside clinical samples.

Blood samples will be analysed for an array of biomarkers with particular interest in early markers with short half-lives. Specifically S100B, Glial fibrillary acidic protein, myelin basic protein, micro-particle analysis and metabolomics assays will be performed. Genetic analysis will be performed initially looking at susceptibility or protective factors with differing mtDNA haplotypes.

*Micro-dialysis*

Intra-cranial pressure monitoring and more lately micro-dialysis catheter monitoring are part of routine clinical care for head trauma allowing monitoring of intra-cranial pressure and brain oxygen tension; important clinical variables. Micro-dialysis is a technique that involves the placement of a catheter containing a semi-permeable membrane into a tissue. A fluid is then circulated over this membrane and small-molecule substances in the tissue will then diffuse across the membrane allowing analysis to be performed to detect those of interest, this fluid is known as a diasylate. Although this technique was first developed 50 years ago it has only recently been adopted into routine clinical practice in certain centers. Presently the diasylate is discarded following bedside measurement of oxygen, however this fluid could provide a wealth of potential biomarkers, we propose to recover the fluid for analysis. Control patients would not be expected to have ICP monitors of micro-dialysis catheters as these are solely used in the setting of neurosurgical problems.

*CSF*

CSF (cerebrospinal fluid) samples may be withdrawn as part of routine clinical management, particularly where extra-ventricular drains or similar have been placed. Where this happens we propose to withdraw an additional sample of CSF for analysis.

*Imaging*

Imaging will be performed on a random selection of patients as detailed below. MRI, MRS, and DTI sequences will be attained. The initial scans will be interpreted using the imaging findings as biomarkers for trauma. Specifically structural and micro-haemorrhages on MRI, N-acetylaspartate (NAA), choline, creatinine, myoinositol with Magnetic Resonance Specroscopy and changes in fractional anisotropy with Diffusion Tensor Imaging as a marker of axonal disruption.

*Outcome Measures*

A marked weakness in previous studies has been the lack of comprehensive outcome assessment as opposed to assessment of injury severity shortly after injury. Outcome following injuries can be very heterogeneous and prognostication is often inaccurate. For this reason all-round assessment of outcome should allow better extrapolation of the clinical usefulness of potential biomarkers.

At follow-up participants will complete a number of psychological and cognitive questionnaires to categorise various aspects of outcome following their injury. Participants will also undergo measurement of TMS motor thresholds before and after a motor learning exercise. EEG will be performed to measure p300 and VEP, ERG will be recorded.

*Cognitive and psychological questionnaires*

The complexity of the brain leads to a wide array of effects following injury. A plethora of tests have been developed to try to capture these and relate to severity of injury. We have selected short questionnaire based tests to focus on the characteristic sequelae of neuro-trauma, cognitive effects including memory, post-traumatic stress symptoms, depression and anxiety. The Test of Memory Malingering TOMM and Neurological assessment battery NAB will be used and will augment those used in routine clinical practice. Outcome will be assessed by scores against published validation populations. High scores indicating abnormality in the domain tested specific to the individual test. TOMM provides validity to other administered tests and is not an outcome measure of itself.

*Neurophysiology*

Many techniques have been developed for and applied to the study of brain disorders and the impact on brain function. A number of neurophysiological techniques may be used to investigate specific pathways or attributes. Trans-cranial magnetic stimulation involves the use of magnetic fields to stimulate specific groups of neurons, the effect of that stimulus may then be measured, for instance in the motor cortex by electro-myogram (EMG) recording of the muscle that area represents. Responses of neurons to the stimulus can be affected by learning activities; the affect of which may be altered following brain injury. Other techniques may be used to study other brain pathways, event related potentials are generalised electrical responses of the brain to a stimulus. p300 is one such potential that may be measured by EEG recording of a subject whilst undertaking a task; the oddball paradigm is an auditory task where-by an unexpected auditory stimulus is introduced allowing the measurement of the p300 potential it triggers. These responses depend on communication between diffuse brain areas and study of them provides insights into that communication in health and disease. These principles have also been applied to the visual system, an electro-retinogram (ERG) may record the retinal response to visual stimuli and a limited version of EEG may record the response of the occipital visual centers to similar stimuli, both can provide important information regarding relevant brain areas following injury.

Outcome will be assessed by results outside of published norms. TMS measurements will look for a loss of the threshold change expected after a learning activity in those suffering the sequelae of head trauma. Outcome for event related potentials will be a delay or absence of the potential.

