   4. *Test Of Memory Malingering (TOMM).* The TOMM is administered by a trained clinical psychologist, it provides a quantification of effort and helps to validate findings of routine clinical questionnaires, it is not transparent to the participant. TOMM score sheet annex l. *Neurological Assessment Battery (NAB)*. A short version is administered which quantifies cognitive sequelae, it is in questionnaire format.
   5. *Trans-cranial Magnetic Stimulation (TMS).* This will be used to explore the neurophysiology behind how the injured brain learns using protocols that are well established and validated in healthy volunteers. Participants will undergo two bouts of single pulse TMS at frequencies no greater than 0.67 Hz before and after a period of learning. The learning task involves seating the participant in front of a computer and tasking them to track a cursor presented on the screen as accurately as possible. For each of the target lines presented, performance will be quantified as root mean square error between the actual and target traces. The change in activation threshold will be measured before and after which provides insight into the underlying changes. This will be performed at 1 year.
   6. *EEG.* The p300 event related potential will be recorded for participants using an auditory oddball paradigm. Latency will be recorded at the scalp electrode with greatest response, EEG itself is as per standard neurophysiological clinical practice. This will be performed at 1 year.
   7. *ERG*. This is recorded using a standard ISCEV protocol for flash and pattern and multifocal stimuli. Participants have three electrodes placed on the forehead and either side of the eyes and a very fine DTL loop electrode placed in the inferior conjunctival fornix which is painless. Recordings of responses to the stimuli are taken following light and dark adaptation. This will be performed at 1 year.
   8. *VEP*. A limited form of EEG is recorded over the occipital cortex to record higher level responses to flash and pattern and multi-focal stimuli, again to the ISCEV standard protocols. This will be performed at 1 year.
   9. *Pupillometry*. This utilises a device to accurately and sensitively assess the pupillary reflexes giving information on the pathways subserved. This will be performed during the first 30 days.
3. Locations:
   1. Sample collection at point of injury will be conducted by West Midlands Ambulance Service.

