   2. Routine blood analysis will be performed as per normal clinical practice by UHB haematology and biochemistry laboratories.
   3. Biomarker assays will be performed at DSTL and UoB.
   4. Genomic analyses will be carried out at UoB
   5. MRI Imaging will be performed in the inpatient MRI department, UHB.
   6. Trans-cranial Magnetic Stimulation, EEG and TOMM will be conducted in the outpatients neurophysiology department of UHB.

Table 1. Schedule of sample analysis

| Time | Sample | Measurement |
| --- | --- | --- |
| 0 (point of injury) | 20mls venous blood | Biomarkers analysis |
| Day 1 (UHB ED) (if no point of injury sample taken) | 20mls venous blood | Biomarkers analysis |
| Day 1 (6-12hrs post injury) | 20mls venous blood | Biomarkers analysis |
| Day 3 | 20mls venous blood | Biomarkers analysis |
| Day 1-14 | Micro-diasylate  CSF (if available) | Biomarkers analysis |
| Day 180 (+/-30) | 20mls venous blood | Biomarkers analysis, Genetic analysis |

Table 2. Schedule of Imaging

| Time | Imaging | Notes |
| --- | --- | --- |
| Day 1-30 | MRI or MRS or DTI | Random selection of patients once stable |
| Day 180 (+/-30) | MRI or MRS or DTI | Same modality as before for comparisom |
| Day 360 (+/-30) | MRS | If 180 day MRS scan abnormal |

Table 3. Schedule of Outcome Measures

| Time | Measures | Notes |
| --- | --- | --- |
| Day 1-30 | Pupillometry | Where possible |
| Day 180 (+/-30) | Cognitive/psychological questionnaires |  |
| Day 360 (+/-30) | Cognitive/psychological questionnaires  TMS  ERP |  |

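### Study Design sets conflicting time limits and none in the control criterion, so at the first blood sample group can be confounded with time since injury

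*Protocol*

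**What the plan says.** All the eligibility statements stand in the protocol's Study Design section.

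- Study-group definition: "patients who have suffered a head injury presenting or transferred to UHB". No time limit.
- Study-group inclusion criterion: a head injury "resulting in presentation to UHB within 1 hour of injury". The hour runs from injury to arrival.
- Control inclusion criterion: "non-head trauma patients matched to control by severity (ISS) and demographic". No time limit. Read literally it also matches controls to controls, although the control-group definition higher up says the matching is to the study group.
- Identification, for patients without distinction of group: "Patients for inclusion will be identified at point of injury or as soon as possible after presentation to UHB upto 1 hour post injury".

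The first blood sample is described elsewhere. Under Methodology, Locations: "Sample collection at point of injury will be conducted by West Midlands Ambulance Service". If that sample is missed, Table 1 provides a fallback, "Day 1 (UHB ED) (if no point of injury sample taken", with no limit in minutes or hours. The next blood sample in Table 1 is timed at 6 to 12 hours after injury, then Day 3 and Day 180.

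**The concern.** The first sample is the study's distinctive early measurement. The section on blood sampling singles out markers that appear early and clear quickly, and for such markers the level depends on when blood is drawn. The comparison of head-injured with other trauma patients is a stated aim under Outcome Measures, and it is the only comparison behind the sample size (80% against 10% with a positive response). Background also accepts that S100B, one of the assayed markers, is not specific to the central nervous system, so some signal in controls is to be expected.

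If one group must reach hospital within the hour and the other need not, the groups may differ in time since injury as well as in brain injury. A difference in marker level at the first sample could then not be attributed to brain injury alone. In addition, staff applying the section cannot tell from it whether a transferred patient, or one bled at scene who arrives after an hour, is eligible.

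**Working it through.** **The plan's own figure.** The inputs in Study Design are 80% and 10% positive, Fisher's exact test, power 0.9, alpha 0.05 and 1:1 allocation, giving 10 per group; sidedness is not stated. Power is the sum, over all pairs (a, b) for which Fisher's p is at most 0.05, of Bin(a; n, 0.8) × Bin(b; n, 0.1).

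- One-sided: 0.888 at n = 9 and 0.937 at n = 10.
- Two-sided: 0.841 at n = 10 and 0.905 at n = 11.

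The stated 10 is reproduced one-sided and is one short two-sided. Time to sample is not an input, so this point does not alter the figure. It bears on what a difference between the groups would mean.

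**The timing statements side by side.**

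| Statement | Whom it covers | What is timed | Limit |
| --- | --- | --- | --- |
| Group definition | Head injury, including transfers | Nothing | None |
| Study-group criterion | Head injury | Arrival | 1 hour from injury |
| Control criterion | Controls | Nothing | None |
| Identification sentence | Patients in general | Identification | 1 hour from injury |
| Table 1, fallback sample | Not split by group | First blood sample | Day 1 only |

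No statement caps the time from injury to first sample in either group.

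**Cases run through the wording** (times are illustrative).

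1. Head injury, bled at scene at 20 minutes, arrives at 75 minutes. The criterion excludes the patient. The group definition includes the patient, and the identification sentence is met because identification took place at point of injury.
2. Head injury, transferred from another hospital, arrives after 1 hour. Included by the definition, excluded by the criterion. To satisfy both, the patient would have to be injured, reach the other hospital and be moved within 60 minutes.
3. Head injury, arrives at 50 minutes, no scene sample, bled later on Day 1. Eligible under every statement, with the sampling time open.
4. Control, first identified at UHB 3 hours after injury. Meets the control criterion, fails the identification sentence.
5. Control, identified within the hour, bled later on Day 1. Eligible under every statement, with the sampling time open.

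Cases 1, 2 and 4 get different answers from different sentences. Case 4, under the control criterion, is the one that separates the groups in time. Cases 3 and 5 show that a common limit on arrival or identification would still leave sampling time uncontrolled.

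**What is affected.** Only the first blood sample. The 6 to 12 hour sample is anchored to injury, Day 3 and Day 180 have their own times, and the primary outcome is the Glasgow Outcome Score at 6 months. The main hypothesis is prognostic, and a prognostic analysis within head-injured patients does not depend on when controls were bled.

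**The case against.** The strongest reply is that the section should be read as a whole. The identification sentence follows the definitions of both groups and is not limited to head injury, Methodology describes one entry route for trauma patients, and Table 1 is one schedule for all. On that reading controls share the hour. This stands in part: it is a fair reading and may be what was meant. But the control criterion does not repeat the limit, and the limit is on identification, so a control found within the hour can still be bled later.

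Three stronger inferences are tempting and are not supported.

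- *That late controls will make a marker look more brain-specific than it is.* If one assumes immediate release, single-exponential decay and controls bled 3 hours later, the remaining fraction is 2^(−3/half-life): 0.125, 0.354 and 0.707 for half-lives of 1, 2 and 6 hours. The half-lives, the delay and the decay model are all assumptions; none is in the protocol. For a marker still rising at the first sample the bias would run the other way. These figures show that timing can matter. They do not estimate a bias.
- *That patients with a sound scene sample are definitely lost.* The criterion read alone excludes them, but the definition and the identification sentence admit them. What the text establishes is a contradiction.
- *That eligibility should rest on a first sample drawn within the hour.* This is a debatable trade. It would drop patients who arrive in time but are bled late. It would also favour those given venous access at scene, because Ethical Considerations permits point-of-injury sampling only where access was placed for clinical reasons.

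Analysis detail may be left to a statistical analysis plan that is not shown. Eligibility limits and matching factors belong in the protocol, and no later analysis can recover patients who were not enrolled.

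**Conclusion.** The point holds as an inconsistency of eligibility wording with a specific statistical consequence. Study Design limits arrival for head-injured patients, sets no limit in the control criterion, and contains two further sentences that do not agree with these. Read as written, controls may be enrolled and first sampled later, so group can be confounded with time since injury at the first blood sample.

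Size and direction are unknown. They depend on transport times, on how often the scene sample is obtained in each group, and on marker kinetics, none of which the protocol gives. If the identification sentence is applied strictly to controls, the imbalance shrinks, but sampling time remains open in both groups. The later bloods and the 6-month outcome are not directly affected. An amendment is worthwhile because the correction is cheap and the early comparison is hard to interpret without it.

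**What to change.** 1. State the same time-from-injury limit in both inclusion criteria, and say what it applies to.
2. Reconcile it with the study-group definition (in particular, whether transferred patients are in), with the identification sentence and with the fallback row of Table 1.
3. Settle in words whether a patient sampled at point of injury who arrives after 1 hour is eligible.
4. Record the time from injury to first research sample in the same way in both groups. Either match on it or adjust for it in the brain versus non-brain comparison of the first sample. Step 1 should come first: if the sampling times of the two groups barely overlap, adjustment is extrapolation.

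The cost is amendment wording, somewhat slower recruitment of controls, one recorded interval per patient and a little more analysis. The sample-size calculation needs no change on this account.
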